**(Amended January 17, 2003)**

## Detailed description of study stages/visits for Cohort 2

**When materials are provided by GlaxoSmithKline Biologicals, it is mandatory that all clinical samples (including serum samples) be collected using exclusively those materials in the appropriate manner. The use of other materials could result in the exclusion of the subject from analysis. The investigator must ensure that his/her personnel and the laboratory(ies) under his/her supervision comply with this requirement.**

The parents/guardians will be instructed to contact the investigator immediately should the child manifest any signs or symptoms any time throughout the study period that the parents/guardians perceive as serious.

| **Clinic Visit 1: Screening** | | |
| --- | --- | --- |
| **Days *–90 to* *-7*~~35 to -7~~: Screening (Amended January 17, 2003)** | | |
| · | | Obtain written/thumb-printed informed consent from the parents/guardians. |
| · | | History taking and physical examination - ***baseline measurement of spleen size, body weight and height or length, as appropriate for age* (Amended January 17, 2003)** |
| · | | Checking of inclusion/ exclusion criteria. |
| · | | Finger prick blood sample collected (2 ml, providing a minimum of 1 ml of serum) for baseline analysis of:   - Haematology : Blood Count (BC) which includes platelets, white blood cells, haematocrit and haemoglobin - Biochemistry (creatinine, bilirubin and ALT) - RF1-like antibodies - Indirect fluorescent antibody test (IFAT) for anti-parasite antibodies |
| **Clinic Visit 2: First vaccination (Day 0)** | | |
| **Day 0: Pre vaccination 1** | | |
| · | | Provision of photo ID |
| · | | Checking of inclusion/ exclusion criteria. |
| · | | History-related physical examination – pre-vaccination axillary body temperature, ~~baseline measurement of spleen size, body weight and height or length, as appropriate for age~~**(Amended August 13, 2002) (Amended January 17, 2003)** |
| · | | Randomization |
| · | | Recording of concomitant medication and bednet use for the previous night. |
| · | | Finger prick blood sample collected (1-2 ml, providing a minimum of 0.5 ml of serum) pre-vaccination for baseline analysis of:   - Serology (anti-HBs and anti-CS antibodies and HBsAg) |
| · | | Intra-muscular (IM) administration of the first vaccine dose in the deltoid region of the left arm. |
| · | | Each vaccinee will be closely observed for one hour or longer if necessary with appropriate medical treatment readily available in case of a rare anaphylactic reaction following the administration of the vaccine. After the observation period, axillary body temperature will be recorded again, and together with any local and general signs and symptoms that may occur, will be recorded in the CRF by the investigator. |
| ***Field worker vaccination follow-up visits 1-3 after first vaccination*** | | |
| ***Days 1, 2 and 3:*** | | |
| · | | Recording of concomitant medication. |
| · | | Reporting of any Serious Adverse Events (SAEs) which the vaccinee has experienced since last visit. |
| · | | Recording of axillary body temperature and any local or general solicited symptoms experienced at time of field worker visit, and within the previous 24 hours, onto diary cards by field workers, on the 3 subsequent days after vaccination. |
| **Clinic Visit 3: Second vaccination (27 to 37 days after Visit 2)** | | |
| **Day 30: Post vaccination 1** | | |
| · | Verification of photo ID and subject number | |
| · | The investigator must record all non-serious adverse events that occurr 1 month (minimum 30 days) post-vaccination 1. | |
| · | Reporting of any Serious Adverse Events (SAEs) which the vaccinee has experienced since the first vaccine dose. | |
| · | Physical examination –pre-vaccination axillary body temperature | |
| · | Checking of elimination criteria and contraindications to vaccination. | |
| · | Recording of concomitant medication. | |
| · | Intra-muscular (IM) administration of the second vaccine dose in the deltoid region of the right arm. | |
| · | Each vaccinee will be closely observed for one hour or longer if necessary with appropriate medical treatment readily available in case of a rare anaphylactic reaction following the administration of the vaccine. After the observation period, axillary body temperature will be retaken, and together with local and general signs and symptoms that may occur, will be recorded in the CRF by the investigator. | |
| ***Field worker vaccination follow-up visits 4-6 after second vaccination*** | | |
| ***Days 31, 32 and 33:*** | | |
| · | Recording of concomitant medication. | |
| · | | Reporting of any Serious Adverse Events (SAEs) which the vaccinee has experienced since last visit. |
| · | | Recording of axillary body temperature and any local or general solicited symptoms experienced at time of field worker visit, and within the previous 24 hours, onto diary cards by field workers, on the 3 subsequent days after vaccination. |
| ***Field worker visit 7: for Active Detection of Infection (14 days pre dose 3)*** | | |
| ***Day 46:*** | | |
| · | Treatment of all subjects with antimalarial (administration of first dose of amodiaquine and SP and provision of following two doses) without checking for parasitaemia | |
| · | | Reporting of any Serious Adverse Events (SAEs) which the vaccinee has experienced since last visit. |
| **Clinic Visit 4: Third vaccination (27 to 37 days after Visit 3)** | | |
| **Day 60: Post vaccination 2** | | |
| · | Verification of photo ID and subject number | |
| · | The investigator must record all non-serious adverse events that occur 1 month (minimum 30 days) post-vaccination 2. | |
| · | Reporting of any Serious Adverse Events (SAEs) which the vaccinee has experienced since the previous vaccine dose. | |
| · | Physical examination –pre-vaccination axillary body temperature . | |
| · | Checking of elimination criteria and contraindications to vaccination. | |
| · | Recording of concomitant medication. | |
| · | Finger prick blood sample collected (0.5-1 ml) for:   - Blood film for parasitaemia determination - ***Parasite genotyping***   **(Amended January 17, 2003)** | |
| · | Intra-muscular (IM) administration of the third vaccine dose in the deltoid region of the left arm. | |
| · | Each vaccinee will be closely observed for one hour or longer if necessary with appropriate medical treatment readily available in case of a rare anaphylactic reaction following the administration of the vaccine. After the observation period, axillary body temperature will be retaken, and together with local and general signs and symptoms that may occur, will be recorded in the CRF by the investigator. | |
| ***Field worker vaccination follow-up visits 7-9 after third vaccination*** | | |
| ***Days 61, 62 and 63:*** | | |
| · | Recording of concomitant medication. | |
| · | | Reporting of any Serious Adverse Events (SAEs) which the vaccinee has experienced since last visit. |
| · | | Recording of axillary body temperature and any local or general solicited symptoms experienced at time of field worker visit, and within the previous 24 hours, onto diary cards by field workers, on the 3 subsequent days after vaccination. |
| ***Field worker visit 10 for Active Detection of Infection (14 days post dose 3)*** | | |
| ***Day 74:*** | | |
| · | Recording of axillary body temperature: if temperature  37.5°C or history of fever, the child will be brought to Ilha Josina Health Facility | |
| · | Surveillance for infection morbidity questionnaire for Cohort 2 completed | |
| · | Finger prick blood sample collected (0.5-1 ml) for:   - Blood film for parasitaemia determination - Parasite genotypingby PCR | |
| · | | Reporting of any Serious Adverse Events (SAEs) which the vaccinee has experienced since last visit. |
| **Clinic Visit 5: Follow-up visit after third vaccination and Cross-sectional Survey (30 to 37 days after Visit 4)** | | |
| **Day 90: Post vaccination 3** | | |
| · | Verification of photo ID and subject number | |
| · | Checking of elimination criteria. | |
| · | Recording of concomitant medication. | |
| · | | Physical examination |
| · | The investigator must record all non-serious adverse events that will have occurred 1 month (minimum 30 days) post-vaccination 3. | |
| · | Reporting of any Serious Adverse Events (SAEs) which the vaccinee has experienced since the previous vaccine dose. | |
| · | | Venous blood sample collected (3 ml, providing a minimum of 1 ml of serum) for analysis of:   - Serology (anti-HBs, RF1-like and anti-CS antibodies) - Haematology : Blood Count (BC) which includes platelets, white blood cells, haematocrit and haemoglobin - Biochemistry (creatinine, bilirubin and ALT) - Blood film for parasitaemia determination - Parasite genotyping by PCR |
| ***Field worker visits 12-17 for Active Detection of Infection (visits every two weeks)*** | | |
| ***Days 104, 118, 132, 146, 160 and 174:*** | | |
| · | Recording of axillary body temperature: if temperature  37.5°C or history of fever, the child will be brought to Ilha Josina Health Facility | |
| · | Surveillance for infection morbidity questionnaire for Cohort 2 completed | |
| · | Finger prick blood sample collected (0.5-1ml) for analysis of:   - Blood film for parasitaemia determination - Parasite genotypingby PCR | |
| · | | Reporting of any Serious Adverse Events (SAEs) which the vaccinee has experienced since last visit. |
| ***Field worker visits 18-19 for Active Detection of Infection  (monthly visits)*** | | |
| ***Months 7 and 8:*** | | |
| · | Recording of axillary body temperature: if temperature  37.5°C or history of fever, the child will be brought to Ilha Josina Health Facility) | |
| · | Surveillance for infection morbidity questionnaire for Cohort 2 completed | |
| · | Finger prick blood sample collected (0.5-1 ml) for analysis of:   - Parasite genotyping by PCR - Blood film for parasitaemia determination | |
| · | | Reporting of any Serious Adverse Events (SAEs) which the vaccinee has experienced since last visit. |
| **Clinic Visit 6: Cross-sectional Survey at Month** 8½ **(146 to 186 days after Visit 5)** | | |
| **Month** 8½**:** | | |
| · | Verification of photo ID and subject number | |
| · | Checking of elimination criteria. | |
| · | Reporting of any Serious Adverse Events (SAEs) which the vaccinee has experienced since the last visit. | |
| · | Recording of concomitant medication. | |
| · | | Recording of bednet use for the previous night. |
| · | Recording of axillary body temperature. | |
| · | | Evaluation of spleen size (classification) and body weight |
| · | | Finger prick blood sample collected (1-2 ml, providing a minimum of 0.5 ml of serum) for analysis of:   - Serology (anti-HBs and anti-CS antibodies) - Haematology : haematocrit - Biochemistry (creatinine, bilirubin and ALT) - Blood film for parasitaemia determination - Parasite genotyping by PCR |
| · | | End of surveillance period for Cohort 2 (double-blind phase) and Study Conclusion |
| ***Field worker monthly follow-up visits 20-32*** | | |
| ***Months 9 to 21:*** | | |
| · | Reporting of any Serious Adverse Events (SAEs) which the vaccinee has experienced last visit. | |
| · | Recording of concomitant medication. | |
| **Clinic Visit 7: Cross-sectional Survey at Month 21 (512 to 568 days after Visit 5)** | | |
| **Month 21:** | | |
| · | Verification of photo ID and subject number | |
| · | Checking of elimination criteria. | |
| · | Reporting of any Serious Adverse Events (SAEs) which the vaccinee has experienced since the last visit. | |
| · | Recording of concomitant medication. | |
| · | Recording of axillary body temperature. | |
| · | | Evaluation of spleen size (classification) and body weight |
| · | | Finger prick blood sample collected (1-2 ml, providing a minimum of 0.5 ml of serum) for analysis of:   - Serology (anti-HBs and anti-CS antibodies) - Haematology : haematocrit - Biochemistry (creatinine, bilirubin and ALT) - Blood film for parasitaemia determination |
| · | | End of follow-up period for safety surveillance and Study Conclusion of single-blind surveillance phase . |

## Clinical examination at cross-sectional surveys

All subjects will be examined at the cross-sectional surveys at months 8½ and 21 to determine their body weights, axillary temperatures and spleen sizes, according to Hackett’s method[[31]](#endnote-32) (see Table 3)

Table 3: Classification of spleen sizes according to Hackett

| Class | Description |
| --- | --- |
| 0 | Normal spleen not palpable even on deep inspiration. |
| 1 | Spleen palpable below the costal margin, usually on deep inspiration. |
| 2 | Spleen palpable below the costal margin, but not projected beyond a horizontal line half way between the costal margin and the umbilicus, measured along a line dropped vertically down from the left nipple. |
| 3 | Spleen with lowest palpable point projected more than half way to the umbilicus but not below a line drawn horizontally through it. |
| 4 | Spleen with lowest palpable point projected below the umbilical level but not projected beyond a horizontal line situated half way between the umbilicus and the symphysis pubis. |
| 5 | Spleen with lowest palpable point beyond the lower limit of class 4. |

## Sample handling and analysis

### Collection of blood samples

Due to the mistrust of the local population to blood sampling by venipuncture, finger prick samples will be obtained whenever possible. Finger pricking will be repeated up to a maximum of three times for each sampling time point (see SOPs at investigator’s site).

### Treatment and storage of biological samples

See Appendix D of the protocol for details of treatment and storage of biological samples.

See Appendix E for instructions for shipment of biological samples.

### Laboratory assays

Additional tests may be performed if deemed necessary by the investigator or GSK Biologicals for the further investigation of the toxicity/immunogenicity of the vaccine. Detailed SOPs governing the assays at the CISM laboratory will be maintained by the Principal Investigator and respective staff team members who will observe the specific SOP requirements. Details of the serological assays can be found in Appendix F.

#### Laboratory testing for Cohort 1

***Laboratory tests at screening: clinic visit 1***

1-2 ml of blood will be obtained from finger prick samples to provide whole blood and a minimum of 0.5 ml of serum for:

- haematology (blood count [BC], which includes platelets, white blood cells, haematocrit and haemoglobin)
- biochemistry (creatinine, ALT, bilirubin)
- indirect fluorescent antibody test for anti-parasite antibodies

***Laboratory tests during the study: clinic visit 2 (day 0)***

1-2 ml of blood will be obtained from finger prick samples to provide whole blood and a minimum of 0.5 ml of serum for:

- serology (HBsAg and anti-CS antibodies)

***Laboratory tests during the study: clinic visit 5 (day 90)***

1-2 ml of blood will be obtained from finger prick samples to provide whole blood and a minimum of 0.5 ml of serum for:

- haematology (blood count [BC], which includes platelets, white blood cells, haematocrit and haemoglobin)
- biochemistry (creatinine, ALT, bilirubin)
- serology (anti-CS antibodies)

***Laboratory tests during the study: clinic visits 6 (month*** 8½***, day 256) and 7 (month 21, day 630)***

1-2 ml of blood will be obtained from finger prick samples to provide whole blood and a minimum of 0.5 ml of serum for:

- haematology (haematocrit)
- biochemistry (creatinine, ALT, bilirubin)
- serology (anti-CS antibodies)
- determination of parasitaemia and parasite density
- ***parasite genotyping by PCR***

**(Amended August 13, 2002)**

#### Laboratory testing for Cohort 2

***Laboratory tests at screening: clinic visit 1***

2 ml of blood will be obtained from finger prick samples to provide a minimum of 1 ml of serum for:

- haematology (blood count [BC], which includes platelets, white blood cells, haematocrit and haemoglobin)
- biochemistry (creatinine, ALT, bilirubin)
- RF1-like antibodies
- indirect fluorescent antibody test for anti-parasite antibodies

***Laboratory tests during the study: clinic visit 2 (day 0)***

1-2 ml of blood will be obtained from finger prick samples to provide a minimum of 0.5 ml of serum for:

- serology (anti-CS and anti-HBs antibodies and HBsAg)

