***Laboratory tests during the study: clinic visit 6 (month 8½, day* *256*)**

1-2 ml of blood will be obtained from finger prick samples to provide whole blood and a minimum of 0.5 ml of serum for:

- haematology (haematocrit)
- biochemistry (creatinine, ALT, bilirubin)
- serology (anti-CS and anti-HBs antibodies)
- determination of parasitaemia and parasite density
- parasite genotyping by PCR

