***Laboratory tests during the study: clinic visit 7 (month 21, day 630)***

1-2 ml of blood will be obtained from finger prick samples to provide whole blood and a minimum of 0.5 ml of serum for:

- haematology (haematocrit)
- biochemistry (creatinine, ALT, bilirubin)
- serology (anti-CS and anti-HBs antibodies)
- determination of parasitaemia and parasite density

Separation of serum from the finger prick or venous blood samples will be performed at the investigator’s centre.

Determination of parasitaemia and parasite density, haematology and biochemistry will be performed at the CISM laboratories. The acceptable reference ranges will be specified in an SOP at the investigator site and in the GSK central study file.

For anti-CS (anti-R32LR) antibody determination, serum samples (minimum 100 µl) will be sent to GSK Biologicals. Aliquots will be sent to Walter Reed Army Institute of Research (WRAIR) USA, for anti-CS antibody testing.

For HBsAg testing, 100 µl serum samples will be sent to GSK Biologicals. Aliquots will be sent to the Microbiology Service at Hospital Clinic, Barcelona, Spain.

For anti-HBs antibody determination, serum samples (minimum 400 µl) will be sent to GSK Biologicals.

For RF1-like antibodies, serum samples (minimum 250 µl) will be sent to GSK Biologicals.

Indirect fluorescent antibody test for anti-parasite antibodies will be performed at CISM according to previously published methods[[32]](#endnote-33),[[33]](#endnote-34). The anti-parasite antibody levels at screening will be assessed to determine the comparability between study areas in terms of malaria transmission intensity.

For falciparum parasite genotyping by polymerase chain reaction, whole blood samples are collected on filter paper and stored at the investigator’s site until analysis.

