**(Amended January 17, 2003)**

In case of insufficient blood sample volume to perform serology assays in Cohort 2, the samples will be analyzed with first priority given to HBsAg testing (where applicable) then anti-HBs testing RF1-like antibody testing and finally anti-CS testing.

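### Cohort 2, day 0: the 0.5 ml serum minimum is 100 µl below the protocol's own assay volumes, and the priority order makes anti-CS the assay that is lost

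*Supplement*

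**What the plan says.** All of the provisions below concern Cohort 2.

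- **Day 0 (section 5.8.3.2, clinic visit 2; repeated in 5.6).** "1-2 ml of blood will be obtained from finger prick samples to provide a minimum of 0.5 ml of serum for" anti-CS, anti-HBs and HBsAg. No biochemistry is listed at this visit.
- **Months 8½ and 21 (5.8.3.2, clinic visits 6 and 7).** "1-2 ml of blood will be obtained from finger prick samples to provide whole blood and a minimum of 0.5 ml of serum for" haematocrit, biochemistry (creatinine, ALT, bilirubin), anti-CS and anti-HBs, together with parasitology. HBsAg and RF1-like antibodies are not measured at these visits.
- **Assay volumes (end of 5.8.3.2).** "For anti-HBs antibody determination, serum samples (minimum 400 µl) will be sent to GSK Biologicals". Anti-CS needs at least 100 µl, HBsAg 100 µl and RF1-like antibodies at least 250 µl. Biochemistry is run at the site laboratory, and no volume is given for it.
- **Shipping (5.8.4).** At least 0.5 ml of serum from each finger-prick sample goes to the sponsor.
- **Short samples (5.8.4).** If volume is insufficient, Cohort 2 samples are analysed "with first priority given to HBsAg testing (where applicable) then anti-HBs testing RF1-like antibody testing and finally anti-CS testing".
- **Endpoints (Synopsis and 10.3.2).** Anti-CS titre at day 0 is a Cohort 2 secondary immunogenicity endpoint.

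**The concern.** A minimum sample volume should be enough for the tests listed against it. At day 0 it is not: a site can follow the specification exactly and still collect a sample that cannot supply all three assays. The rationing rule in 5.8.4 is written for samples that turn out insufficient, but here a sample that meets the specification is already insufficient. Because anti-CS comes last, the loss always falls on the antibody response to the malaria component. A pre-vaccination sample cannot be collected later.

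Months 8½ and 21 raise a related but weaker question. Three quantities coincide at 0.5 ml: the collection minimum, the shipping minimum and the serology requirement. The plan does not say where the serum for safety chemistry is to come from.

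**Working it through.** **Inputs.** The assay volumes, the assays per visit and the minimum serum are from 5.8.3.2. The order of testing is from 5.8.4.

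**Requirement against minimum.** Need = sum of the stated volumes for the serology assays at that visit; margin = minimum serum − need.

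| Visit (Cohort 2) | Serology need | Minimum serum | Margin |
|---|---|---|---|
| Day 0 | 100 (HBsAg) + 400 (anti-HBs) + 100 (anti-CS) = 600 µl | 500 µl | −100 µl |
| Day 90 (venous) | 400 (anti-HBs) + 250 (RF1-like) + 100 (anti-CS) = 750 µl | 1000 µl | +250 µl, before chemistry |
| Month 8½ | 400 + 100 = 500 µl | 500 µl | 0, before chemistry |
| Month 21 | 400 + 100 = 500 µl | 500 µl | 0, before chemistry |

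The stated 0.5 ml is thus reproduced exactly for months 8½ and 21 on serology alone. It is not reproduced for day 0.

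**Allocation at day 0 in priority order.**

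- A sample of 500 µl: 500 − 100 (HBsAg) − 400 (anti-HBs) = 0 µl left for anti-CS.
- A sample of 599 µl: 599 − 500 = 99 µl left, still below the 100 µl minimum.
- A sample of 600 µl: 100 µl left, which is just enough.

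The compliant samples affected are therefore those from 500 to 599 µl.

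**Comparison with Cohort 1.** Cohort 1 has the same 0.5 ml minimum at day 0 but needs only HBsAg and anti-CS: 100 + 100 = 200 µl. The Cohort 2 visit adds 400 µl for anti-HBs under an unchanged minimum.

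**Blood needed for 0.6 ml of serum.** The protocol's other Cohort 2 specifications give two ratios: 2 ml of blood for 1 ml of serum at screening, and 3 ml for 1 ml at day 90. At these ratios 0.6 ml of serum takes 0.6 × 2 = 1.2 ml to 0.6 × 3 = 1.8 ml of blood. Both lie inside the 1-2 ml range already allowed. The ratios are specification minimums, so actual yields may be better.

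**Chemistry at months 8½ and 21.** With no stated volume, I assume 50 to 200 µl for illustration, taken out of the 500 µl before serology.

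- 50 µl: 500 − 50 − 400 = 50 µl left, too little for anti-CS.
- 100 µl: 500 − 100 − 400 = 0 µl left for anti-CS.
- 200 µl: 500 − 200 = 300 µl, too little even for anti-HBs (400 µl).

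Under that assumption the total need is 0.55 to 0.70 ml. If chemistry serum is additional to the 0.5 ml, serology is covered exactly.

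**The case against.** **The 0.5 ml is a floor, and short samples are foreseen.** A draw of 1-2 ml may yield more, section 5.8.1 allows up to three finger pricks per time point, and 5.8.4 deliberately protects the hepatitis B assays. This stands as a limit on how often the problem arises. It does not reconcile the day-0 figures, because the protocol accepts 0.5 ml as adequate for tests that need 0.6 ml.

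**The consequence is modest.** This stands.

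- Anti-CS is analysed descriptively in 10.7.4 (seropositivity rates and GMTs with confidence intervals).
- No change from baseline is planned, and baseline anti-CS is not among the efficacy covariates in 10.7.2.2.7.
- Anti-CS is also measured in the 1564 Cohort 1 children at the same time points.
- The day-90 post-vaccination sample is adequate for serology.

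**A reader might infer that all three finger-prick visits fall short.** The documents do not support this. At months 8½ and 21 the stated serology volumes equal the minimum. The text can also be read as 0.5 ml net for serology, with chemistry done separately at the site. A shortfall there depends on a volume that the plan does not give.

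**A reader might also infer a biased comparison between arms.** This is not shown either. The day-0 sample is taken before vaccination, so loss at that visit should not depend on the allocated vaccine. Loss concentrated in children who are hard to bleed is plausible but undocumented.

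**Conclusion.** The day-0 minimum for Cohort 2 is wrong by the protocol's own figures: 600 µl is needed and 500 µl is accepted. The 100 µl deficit equals the whole anti-CS requirement. Compliant samples of 500 to 599 µl lose the baseline value of a secondary endpoint. All 416 Cohort 2 children are sampled at this visit, but that is the number exposed to the rule and not an estimate of the number lost; the documents give no distribution of serum yields.

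Months 8½ and 21 have zero margin before chemistry. Whether they fall short cannot be settled from the documents.

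The day-0 result assumes that the aliquots passed on to the other laboratories come out of the stated volumes. The plan does not say so; if they are additional, the deficit is larger. The effect on the trial's conclusions is small, but the error is clear and cheap to correct before sampling starts.

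**What to change.** - **Day 0.** In sections 5.6 and 5.8.3.2, raise the Cohort 2 serum minimum at clinic visit 2 to at least 0.6 ml, keeping the 1-2 ml draw. In 5.8.4, raise the finger-prick shipping minimum for that visit to match.
- **Months 8½ and 21.** Set the collection minimum at 0.5 ml for serology plus the volume the site laboratory needs for creatinine, ALT and bilirubin, and state that volume.
- **Aliquots.** State whether those for the other laboratories are included in the listed assay volumes.

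The specification used for the Cohort 2 screening finger prick ("2 ml of blood will be obtained from finger prick samples to provide a minimum of 1 ml of serum for" its baseline tests) would also cover these visits on the stated volumes, but it asks for more than the documented 0.1 ml deficit requires.

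The cost is protocol wording and no new procedure. The downside is that some children must give a slightly larger finger-prick yield, in a community where 5.8.1 records mistrust of venous sampling and caps the number of pricks.
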